## 8. Provisions to Monitor the Data to Ensure the Safety of Subjects

*This study involves no more than minimal risk study and this section is not required.* ☐ **N/A**

*The plan might include establishing a data monitoring committee and a plan for reporting data monitoring committee findings to the IRB and the sponsor.*

- a. *Describe the plan to periodically evaluate the data collected regarding both harms and benefits to determine whether subjects remain safe.*

The data and safety monitoring plan (DSMP) for this trial focuses on close monitoring of infant growth by the principal investigators (PIs) in conjunction with a Data and Safety Monitoring Board (DSMB), along with prompt reporting of excessive adverse events and any serious adverse events to the NIH/NIDDK and to the Institutional Review Board (IRB) at Augusta University (AU). Because behavioral interventions aimed at reducing rapid weight gain could theoretically result in insufficient weight gain by study participants, individual participant growth will be closely monitored by the investigators. The adverse event form, which we used in our previous studies, meets the goals of this plan.

In this study, an adverse event shall be defined as any detrimental change in the participant's condition, whether it is related to study interventions, study outcomes, or to another unrelated illness. Adverse effects may be (a) unrelated to the study interventions or (b) potentially related to the study interventions.

### *Adverse Events Unrelated to the Study Interventions:*

Adverse events due to illnesses unrelated to study interventions may be grounds for withdrawal if the illness is considered significant by the study investigators or if the participant is no longer able to effectively participate in the study. A significant illness would be one that would compromise the child's ability to function normally and thrive, such as the diagnosis of a

malignancy, illness characterized by growth problems, disease requiring ongoing and intensive treatment, and/or one requiring repeated hospitalizations or physician visits. Subjects experiencing routine, minor, self-limited acute illnesses that typically occur during infancy and do not affect long-term growth will not be recorded, and the child will continue to participate in the study. Examples of minor illnesses include acute otitis media, bronchiolitis, upper respiratory infections, urinary tract infections, and gastroenteritis. Medications for acute, self-limited illnesses such as those stated above will not be recorded, but chronic medication use (> 1 month) will be recorded.

Other adverse events that could affect growth include a milk-protein allergy, other food allergies, or physician-diagnosed gastroesophageal reflux disease (GERD) requiring medication. Surgical conditions such as intestinal malrotation and pyloric stenosis also would impact infant feeding and weight gain. Therefore, these will be recorded and if the participant's physician determines that these conditions can affect long-term growth, the participant will be withdrawn from the study. Documentation of an adverse event unrelated to study interventions that are not considered minor illnesses of childhood and those that can significantly affect growth will be recorded on an Adverse Event Report Form and will include the following information:

1. Description of the illness
2. Dates of illness
3. Treatment of illness and dates (medications, doses, and dose frequency)
4. Whether emergency treatment or hospitalization was required
5. Treatment outcome

#### *Adverse Events Potentially Related to the Study Interventions:*

It is theoretically possible that behavioral interventions designed to prevent rapid weight gain during infancy could result in underfeeding by parents and insufficient growth. The NIH-funded studies that serve as the foundation for the current project did not find an association between study interventions and these adverse events. While the results of these previous projects are reassuring, weight status and growth will be closely monitored and evaluated at frequent intervals in the proposed project in order to monitor the study intervention for potential adverse events. In the current study, there are several ways a potential adverse event related to growth will be identified:

1. Diagnosis by a treating primary care provider (PCP) of insufficient growth or failure to thrive
2. Weight-for-age below the 5th percentile using growth charts from the WHO
3. Downward crossing of two major percentile lines between any two study visits on the WHO weight-for-age growth chart statistically evaluated as a -0.67 Z-score change in order to provide a consistent measure across subjects

For the PCP diagnosis portion of identifying potential adverse events, the study's informed consent document will include information indicating that the study team will communicate with the participant's PCP. Because all participants are infants, it is expected that they will all have a PCP or office where they receive their medical care as is typical for infants. The study team will ensure lines of communication exist with PCPs in addition to the growth monitoring performed as part of the study. To establish the lines of communication between the study team and the PCPs, upon participant randomization, PCPs will be notified that their patients are participating in a study that includes an intervention arm designed to reduce rapid weight gain during the first 16 weeks after birth. A brief description of the study will be shared with them as well as a contact number to call the study team should the PCP become concerned about insufficient growth by their patient. Recognizing that growth monitoring is typically performed at all regularly scheduled primary care appointments, we will ask PCPs for their collaboration in monitoring infant growth in that we would like to be alerted to any concerns that their patient is demonstrating insufficient weight gain. In turn, the study team will report

to the PCP if we determine that their patient meets one of the two screening criteria above when assessed at study visits at 2 weeks, 8 weeks, 12 weeks, or 16 weeks.

During each study visit, home visit staff will calculate weight and length percentiles, and each child's growth chart will be plotted to allow for identification of potentially concerning growth patterns in real time. The infant's growth will be plotted on the WHO charts. The PIs will review growth charts at least twice monthly and then contact the PCPs by phone when appropriate after each individual is closely evaluated as described below. For any individual child that meets initial screening criteria for growth concerns, numerous factors will be considered in determining whether the child's growth is problematic and/or related to study interventions. Examples of such factors include genetic potential based upon parental size, the participant's linear growth, feeding mode (breast milk vs. formula), and interval illnesses. If either the primary care provider or the study investigators believe that it is possible that these growth patterns are a negative result from study participation, the child will be withdrawn from the study.

#### *Expected Rates for Failing Screening Criteria for Adverse Events Potentially Related to Study Interventions*

Using standard population distributions, it is expected that 5% of children will be below the 5th percentile on the weight-for-age growth chart. For downward crossing of two major centile lines, it is expected that this will occur with some frequency given the well-established phenomenon of regression to the mean, which suggests that those born at the higher percentiles have a higher probability of moving downward to the population mean. The results of our pilot study suggest that 15% of participants may experience this, and that will serve as the cut-off alarm value for this study. Combined, these two screening criteria allow for up to a 20% adverse event rate for those events potentially related to the study interventions.

- b. Describe what data are reviewed, including safety data, untoward events, and efficacy data.*

As described above, adverse events reports and infant growth will be monitored.

- c. Describe how the safety information will be collected (e.g., with case report forms, at study visits, by telephone calls with participants).*

We plan to collect adverse event data from the intervention and control groups as they occur using adverse event reports.

- d. Describe the frequency of data collection, including when safety data collection starts.*

Safety data collection will begin immediately after the study commences. We plan to collect adverse event data from the intervention and control groups as they occur, and will report them quarterly. As noted above, the PIs will review growth charts at least twice monthly.

- e. Describe who will review the data.*

Because our proposal includes vulnerable populations (i.e., African American infants and their mothers), we will include a Data Safety Monitoring Board (DSMB). The DSMB will be chaired by a pediatrician with expertise in patterns of normal and abnormal growth in infants (this individual will also serve as the Safety Officer for the study), and will also include a biostatistician as well as researchers with expertise in issues relating to African American families, infant and family behavioral interventions, and maternal health and infant development.

- f. Describe the frequency or periodicity of review of cumulative data.*

We will continuously monitor adverse event rates in all participants. In consultation with PI [name], PI [name] will have primary responsibility for reporting Adverse Events, Serious Adverse Events, and Unanticipated Problems to the AU IRB, the study's DSMB, and the NIH/NIDDK as required. PI [name] will have secondary responsibility for reporting.

Safety reports will be sent to the study statistician, the PIs, and the Safety Officer/Chair of the DSMB quarterly. At least once per year, the DSMB will convene to review study progress and issues related to the safety of the study interventions. Meetings may be more frequent than once per year if the need for such meetings becomes apparent to the Safety Officer, PIs, IRB, or NIH/NIDDK. The project coordinator will be responsible for assembling the data and producing these reports in conjunction with the study statistical team, as well as assuring that all parties obtain copies of these reports.

*g. Describe any conditions that trigger an immediate suspension of the research.*

#### *Stopping Rules.*

As outlined above, we will continuously monitor adverse event rates in all participants. The safety officer, together with the study investigators, will alert the IRB and the NIH if a greater than or equal to 20% adverse event rate potentially due to study interventions should occur in the treatment group or if significant differences between treatment groups occur.

As described in detail above, we will closely monitor rates of insufficient growth for individual infants and by study treatment group. In addition to individual level monitoring, the study statistician will analyze rates of insufficient growth by treatment group on a quarterly basis. If there are significantly more children with inadequate growth in the intervention group at any point, these data will be presented to the AU IRB, the study's DSMB, and NIH/NIDDK so that a decision can be jointly made as to whether the trial needs to be suspended.

We acknowledge that there are other situations that could occur that might warrant stopping the trial. We have a section on the safety report entitled 'Other situations that have occurred since the last safety report that warrant discussion' to allow for communication of concerns to the study PIs, statistician, and the Safety Officer.

## 9. Withdrawal of Subjects

☐ N/A

*a. If applicable, describe anticipated circumstances under which subjects will be withdrawn from the research without their consent.*

☐ N/A

Any participant with a physician-diagnosed serious adverse event related to the study interventions will be discontinued from the study. Should insufficient weight gain be detected and the cause of this weight gain is potentially related to the study interventions as determined by the PIs after consultation with the participant's primary care provider, the participant will be discontinued from the study. Other non-minor concurrent illnesses or major changes in the family social environment would also lead to discontinuation as determined by the investigators alone or in consultation with the PCP.

*b. If applicable, describe any procedures for orderly termination.*

☐ N/A

In the event that a subject is withdrawn from the research without their consent (whether due to unforeseen change in meeting inclusion criteria or an adverse event), all contact with subject will be ceased. Subjects will receive monetary compensation only for those appointments and study requirements met until the date of withdrawal. Any materials provided (bassinet, intervention materials) as part of the study procedures will remain

|                                                                                                                                                                                                                                                                                                                                                                                                                                                                                                                                                                                                                                                                                                                                                                     |                              |
|---------------------------------------------------------------------------------------------------------------------------------------------------------------------------------------------------------------------------------------------------------------------------------------------------------------------------------------------------------------------------------------------------------------------------------------------------------------------------------------------------------------------------------------------------------------------------------------------------------------------------------------------------------------------------------------------------------------------------------------------------------------------|------------------------------|
| with the subject. Only if agreed to at the time of consent, data collected for that subject dyad until the date of withdrawal will remain part of the study data and included in researcher analysis where possible.                                                                                                                                                                                                                                                                                                                                                                                                                                                                                                                                                |                              |
| 
c. If applicable, describe procedures that will be followed when subjects withdraw from the research, including partial withdrawal from procedures with continued data collection.
 
In the event when subjects withdraw from the research, all contact with subject will be ceased. Subjects will receive monetary compensation only for those appointments and study requirements met until the date of withdrawal. Any materials provided (bassinet, intervention materials) as part of the study procedures will remain with the subject. Only if agreed to at the time of consent, data collected for that subject dyad until the date of withdrawal will remain part of the study data and included in researcher analysis where possible.
 |  N/A |

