For any individual child that meets initial screening criteria for growth concerns, numerous factors will be considered in determining whether the child's growth is problematic and/or related to study interventions. Examples of such factors include genetic potential based upon parental size, the participant's linear growth, feeding mode (breast milk vs. formula), and interval illnesses. If either the primary care provider or the study investigators believe that it is possible that these growth patterns are a negative result from study participation, the child will be withdrawn from the study.

Additional details regarding growth monitoring are included in Section 8 (Provisions to Monitor the Data to Ensure the Safety of Subjects) below.

*d. Describe the duration of an individual subject's participation in the study and the time involved:*

Mother-infant dyads are enrolled for a period of 16 weeks. Interactions include initial enrollment and 4 subsequent research and/or intervention visits to the family's home. Enrollment will take place within 24-72 hours of delivery (while the mother is admitted to the newborn nursery) and participation will continue until the infant is 16 weeks (not more than 30 weeks) of age. Initial enrollment procedures will take 60-90 minutes; each following study visit will take 90-120 minutes.

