## **7. Data and Specimen Management**

a. Describe the data analysis plan, including any statistical procedures:

☐  
N/A

Data analysis will be led by [name], who has expertise in the analysis of longitudinal data. [name]., Assistant Research Scientist and Statistician at CFR, will provide statistical support for the conduct of analyses. All primary statistical analyses will invoke the intent-to-treat paradigm, analyzing data based on randomized assignment. Missing data will be handled using full-information maximum likelihood methods, which use all available information to estimate parameters, making this approach more efficient and less biased than other methods when data are missing at random. All models considered allow for the inclusion of relevant covariates. Covariates to be considered in refining the analyses, in addition to those described in detail in the proposed analyses below, include demographic factors (e.g., maternal employment and hours worked, gestational diabetes), weight-related factors (e.g., maternal pre- pregnancy weight/BMI, gestational weight gain, maternal smoking), and intervention-related factors (e.g., implementation quality, coparent involvement in intervention). We will also examine (1) infant sex as a covariate, given different growth charts for boys and girls and (2) feeding mode as a covariate, given differences in weight gain between breastfed and formula-fed infants.

**Specific Aim 1: The Effects of Sleep SAAF on Infant Weight and Rapid Weight Gain.** In Specific Aim 1 the primary outcomes are infant weight and changes in weight. BMI is generally assumed to be the standard growth measure for assessing obesity-risk in children age 2 years and older, but there is not one universally accepted measure for children younger than age 2 years. Recent data suggests that infant BMI at age 2 months is more strongly associated with obesity at age 2 years than is weight-for-length. Accordingly, BMI z scores will be our primary outcome, but we will also consider models that examine a range of other weight outcomes, including weight for length z-scores, percentiles, and weight for age z-scores; we anticipate that change across different indices of weight gain will be highly correlated and lead to similar conclusions in tests of program impact as well as tests of potential moderators and the hypothesized mediational model.

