
|                                                                                                                                                                                                                                                                                                                                                                                                                                                                                                                                                                                                                                                                                                                                                       |                                 |
|-------------------------------------------------------------------------------------------------------------------------------------------------------------------------------------------------------------------------------------------------------------------------------------------------------------------------------------------------------------------------------------------------------------------------------------------------------------------------------------------------------------------------------------------------------------------------------------------------------------------------------------------------------------------------------------------------------------------------------------------------------|---------------------------------|
| 
The primary outcomes for this study will be BMI z scores at 16 weeks (Specific Aim 1) and parent and infant behaviors at 8 weeks and 16 weeks (Specific Aim 2). We used G Power 3.1.9.2 to estimate the smallest intervention effect size we can detect with 80% power, a 5% two-tailed Type 1 error rate, and two groups of 175 each (conservatively assuming 10% attrition over the course of the study). We can achieve 80% power with an effect size <math>d</math> of 0.34. Our recent research showed an effect size of approximately 0.4 for infant nighttime sleep duration at 8 weeks and for infant conditional weight gain at 6 months, suggesting that we will have sufficient power in our sample to detect intervention effects.
 |                                 |

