| 
b. If applicable, describe any procedures for orderly termination.
 
In the event that a subject is withdrawn from the research without their consent (whether due to unforeseen change in meeting inclusion criteria or an adverse event), all contact with subject will be ceased. Subjects will receive monetary compensation only for those appointments and study requirements met until the date of withdrawal. Any materials provided (bassinet, intervention materials) as part of the study procedures will remain with the subject. Only if agreed to at the time of consent, data collected for that subject dyad until the date of withdrawal will remain part of the study data and included in researcher analysis where possible.
 | 
 N/A
 |
| 
c. If applicable, describe procedures that will be followed when subjects withdraw from the research, including partial withdrawal from procedures with continued data collection.
 
In the event that subjects withdraw from the research, all contact with subject will be ceased. Subjects will receive monetary compensation only for those appointments and study requirements met until the date of withdrawal. Any materials provided (bassinet, intervention materials) as part of the study procedures will remain with the subject. Only if
                                                                                                                                                                                            | 
 N/A
 |

|                                                                                                                                                                                            |  |
|--------------------------------------------------------------------------------------------------------------------------------------------------------------------------------------------|--|
| agreed to at the time of consent, data collected for that subject dyad until the date of withdrawal will remain part of the study data and included in researcher analysis where possible. |  |
|--------------------------------------------------------------------------------------------------------------------------------------------------------------------------------------------|--|

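### Section 9.c gives one rule for withdrawal, ending all contact, and offers no way to stop the sessions yet keep the 16-week weight and length

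*Supplement*

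**What the plan says.** The prompt for section 9.c (Withdrawal of Subjects) asks for the procedures when subjects withdraw, "including partial withdrawal from procedures with continued data collection". The answer in the latest version is "In the event that subjects withdraw from the research, all contact with subject will be ceased". The earlier version in the supplement has the same rule, differing by one word: "In the event when subjects withdraw from the research, all contact with subject will be ceased". The rest of the answer covers payment, materials and data already held. The last are kept on a condition: "Only if agreed to at the time of consent, data collected for that subject dyad until the date of withdrawal" stay in the study data.

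The relevant context in the latest version is as follows.

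- **Timing.** Randomisation is at the 7-10 day home visit, programme sessions are at 3 and 8 weeks, and the 16-week visit is assessment only (sections 6.a and 6.b).
- **Outcome.** The Aim 1 primary outcome is BMI z at 16 weeks (section 7.b).
- **Analysis.** Section 7.a states: "All primary statistical analyses will invoke the intent-to-treat paradigm, analyzing data based on randomized assignment". Missing data are handled by full-information maximum likelihood, described as "more efficient and less biased than other methods when data are missing at random".
- **Blinding.** Section 6.c says the study is not blinded.
- **Reduced-contact option.** Section 6.a offers a no-contact 16-week visit, but only to 24 dyads affected by COVID-19 restrictions. It collects infant weight without length.

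**The concern.** The form asks about the middle case and the answer covers only the extreme one. A mother may be unwilling to continue with the sessions yet content to have her infant measured once more. The protocol gives staff no instruction to offer her that, and a literal reading of 9.c ends follow-up as soon as she says she is withdrawing.

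Any such withdrawal comes after randomisation and before the primary outcome. One arm is coached not to use feeding as the default response to crying, while the other receives child-safety content. A decision to leave could therefore depend on the assigned programme and be related to feeding, and so to weight. Intent-to-treat analysis keeps infants in their assigned arm but cannot supply a 16-week value that was never measured. The likelihood method fills that gap only under missing at random. It also draws on earlier weights, which 9.c keeps only with prior agreement. The 10% attrition allowance in section 7.b protects precision and does nothing about bias.

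**Working it through.** **1. The plan's own figure.** Section 7.b gives a detectable d of 0.34 for 80% power, two-sided 5%, two groups of 175 and 10% attrition. Using d = (1.960 + 0.842) × √(2/n):

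- n = 175 × 0.9 = 157.5 gives d = 0.316
- n = 175 gives d = 0.300
- n = 135 (the earlier version's 150 less 10%) gives d = 0.341

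The stated 0.34 matches the earlier group size, not the current one. That discrepancy is conservative and does not affect this point. I use 0.34 below only as the plan's yardstick.

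**2. Inputs for the bias illustration.** The documents give no voluntary withdrawal rate and no reasons by arm, so these are assumptions:

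- w, the share of the intervention arm unmeasured at 16 weeks: 5% or 10% (about 9 or 18 of 175 infants)
- D, the difference in SD units between unmeasured and measured infants that remains after modelling: 0.25, 0.5 or 1.0
- control arm: 10% loss, unrelated to outcome

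Bias = w × D. The standard error is √(1/[175(1−w)] + 1/157.5). Power is for a true d of 0.34 with the bias running against the effect. With no bias it is 85.5% at 157.5 per group.

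| w | D | Bias (SD) | Share of 0.34 | Two-sided type I error | Power |
|---|---|---|---|---|---|
| 5% | 0.25 | 0.0125 | 4% | 5.1% | 83.8% |
| 5% | 0.5 | 0.025 | 7% | 5.6% | 80.9% |
| 5% | 1.0 | 0.05 | 15% | 7.3% | 74.2% |
| 10% | 0.25 | 0.025 | 7% | 5.6% | 79.8% |
| 10% | 0.5 | 0.05 | 15% | 7.3% | 73.0% |
| 10% | 1.0 | 0.10 | 29% | 14.4% | 56.7% |

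**3. What recovering some measurements would do.** Take w = 10% and D = 0.5, so bias = 0.050, and suppose half of the missing infants are measured after all.

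- Recovered infants typical of all those missing (gap 0.5): the measured mean shifts by 0.05 × 0.5 / 0.95 = 0.026. The bias falls to 0.050 − 0.026 = 0.024, about half.
- Recovered infants less different (gap 0.25, the rest 0.75): the shift is 0.05 × 0.25 / 0.95 = 0.013. The bias falls to 0.037, a reduction of about 26%.

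**4. Precision.** If all of the 10% attrition were recovered, n per group would rise from 157.5 to 175 and power at d = 0.34 from 85.5% to 88.9%. The precision gain is modest; the main reason to act is possible bias.

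**The case against.** The strongest reply is that 9.c governs withdrawal from the research as a whole, and ceasing contact then is ordinary respect for the mother's decision. Nothing says that declining or missing a session is withdrawal. Other sections are compatible with continued follow-up: research and intervention visits are distinguished, the 16-week visit delivers no programme content, a 12-week call reminds mothers of it, and it carries its own payment of $100. The 9.c prompt is also conditional on applicability. This stands in part. A reader might infer that a mother who dislikes the sessions is forced out of the weigh-in, and the documents do not say so. What remains is that, asked directly about partial withdrawal, the protocol offers none here or elsewhere.

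A reader might also take visit length as a cause of unequal loss. Section 6.d says "each following study visit will take 90-120 minutes", but that applies to both arms and to research visits as well. It is a burden, not evidence of differential withdrawal. Only the difference in content could act by arm, and the documents do not report it as a reason for leaving.

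The bias figures rest on assumed inputs. Attrition includes families who move or cannot be reached, so 10% voluntary loss in one arm is an upper illustration. Baseline weight and any retained earlier weights reduce the part the model cannot see. Outcome-related loss in the control arm could offset some of the rest. All of this stands.

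Finally, the consent pages are not in the review copy and may already offer graded withdrawal. That bears on whether the consent wording needs changing, not on the text of 9.c.

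**Conclusion.** The point holds as a gap in 9.c that is cheap to close. The stated rule gives up 16-week outcomes that some withdrawing mothers might agree to provide, in an unblinded intent-to-treat trial whose missing-data method depends on missing at random. The documents do not show that the comparison is biased, or that leaving the sessions ends follow-up. The size cannot be estimated from them. The range of about 0.01-0.10 SD (4% to 29% of the stated 0.34) is an illustration. It assumes 5-10% missing in one arm, an unmodelled gap of 0.25-1.0 SD and no offsetting loss in the other arm. Recovering some infants would reduce such a bias, by about half only if half are recovered and they are typical of all those missing. The point concerns the mother's own choice; withdrawal by the investigators is a separate matter.

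**What to change.** Amend 9.c, and the consent wording if it does not already provide this, so that a withdrawing mother may choose between two levels:

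1. stop sessions and questionnaires, but allow a short 16-week visit for infant weight and length;
2. stop everything, with no further contact.

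State that missing or declining sessions alone is not withdrawal from the research. Record the level chosen and the reason, and report both by arm so that readers can judge the missing-at-random assumption. Analyse level-1 infants in the arm to which they were randomised. The short visit must include length, because BMI z cannot be calculated from weight alone.

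The cost is an amendment to the protocol and possibly the consent form, plus a brief measurement at a time point already scheduled for every dyad. The downside is limited extra contact, with permission, with families who have left the programme.
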